### Data analyses

#### Outcome evaluation – statistical (quantitative) analysis

The primary outcome will be the difference between the intervention and comparator groups in mean steps per day at 6 months. For all secondary outcomes, we will also examine differences between intervention and comparator groups in mean change at 6 months. The additional follow-up data collected from Health*e*Steps™ group will allow us to evaluate: i) feasibility of retaining individuals for an extra 6 and 12 months (to inform a larger study); and ii) within group change to 12 and 18 months to determine the sustainability of any positive changes (in health behaviours and health indicators) observed following the active phase.

We will analyze data based on an intent-to-treat approach; thus, we will include all participants with at least valid baseline data according to the randomization scheme. We will analyze data using linear or generalized linear mixed models for repeated measurements and we will retain the baseline outcome as part of the outcome vector and constrain the group means as equal because of randomization [50]. This approach is equivalent to analysis of covariance approach, but has the advantage of including subjects with missing data [51]. For all models, we will examine differences between groups at 6 months and changes within groups from baseline to 6 months (and to 12 months and 18 months for the intervention group). Terms included in models will include time, treatment (group) × time, age and site. Time will be modeled categorically with indicator variables (with baseline as the reference category). Residuals from models will be examined and subject to assumptions checks.

To address participant dropout, we will also compare baseline characteristics of participants who dropped out versus participants who were included in the analysis. Interpretation of study results will primarily be based on estimation and associated 95% confidence intervals [50]. Confidence intervals for differences excluding zero or two-sided p-values less than 0.05 will be reported as statistically significant. Analyses will be performed using SAS version 9.4 (SAS Statistical Analysis Software).

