**Fig. 1 Fig1:**
[figure not shown]
HealtheSteps Flow Diagram

Study recruitment will begin in May 2015 at the 5 clinic sites, with the intervention starting in June 2015. Western University Health Sciences Research Ethics Board approved this study and all participants will provide written informed consent. The pragmatic RCT portion of this study was registered on April 6, 2015 with ClinicalTrials.gov (identifier: NCT02413385).

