#### Maintenance phase II (months 12–18)

Participants will no longer have access to the online Tyze Personal Networks, and Sykes phone coaching services, but will still have access to the publicly available resources, including the HealtheSteps™ and eaTracker Smartphone apps, and the Health*e*Steps™ website.

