### Comparator group (wait-list control)

This group will continue with usual activities without intervention from the study team for the first 6-month period. After the 6 month measurement sessions are completed, participants allocated to this group will be given the opportunity to start the 6-month Health*e*Steps™ program.

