### Data collection

#### Outcome evaluation

The outcome measures will be taken at baseline and 6 months in both groups, and then again at 12 and 18 months in the intervention group only (see Table 1). Home visits will be conducted when participants are unable to attend follow-up measurement sessions at the sites to increase participant retention throughout the long-term follow-up. Data sources will include self-reported PA, participant demographics, clinical measures, and the completion of health related information and questionnaires (See Table 2).

**Table 1 Tab1:** Screening and measurement sessions schedule

Measurement	Screening	Baseline	6-month	12-month (Intervention Group only)	18-month (Intervention Group only)
*Screening & Eligibility Measures*					
Participant Self-Reports at Screening	X				
Pre-Randomization ID #	X				
Letter of Information & Consent Form	X			X	
PAR-Q	X				
Health Care Provider Clearance Form	X				
Eligibility Form	X				
Group Allocation		X^a^			
Participant ID#		X^a^			
*Baseline Health Information*					
Demographics & Health Related Information		X			
*Clinical Measures*					
Age	X	X^b^			
Height	X	X^b^	X^b^	X^b^	X^b^
Weight	X	X^b^	X	X	X
Body Mass Index	X	X^b^	X	X	X
Waist Circumference		X	X	X	X
Blood Pressure		X	X	X	X
*Self-Reported Physical Activity*					
Average Steps/day (Step Count Outcome Tracking Form)		X	X	X	X
International Physical Activity Questionnaire		X	X	X	X
*Self-Reported Eating*					
Modified DINE		X	X	X	X
Starting the Conversation		X	X	X	X
*Health-Related Quality of Life*					
EQ-5D-3 L		X	X	X	X

^a^Occurs at Randomization & Allocation Session

^b^Use number recorded at Screening Session

**Table 2 Tab2:** Data collection & measurement protocol

Outcome Measure	Equipment required	Protocol
*Self-Reported Physical Activity*		
Average steps/day	Pedometer (Yamax Digiwalker SW-200 with security strap)	• Participants wear pedometers during waking hours for a 7-day period (putting pedometer on upon waking and removing immediately before sleeping), but not during showering/bathing • Participants are asked to wear the pedometer at the waist, centered over their most dominant foot • Participants record the number of steps completed each day on a paper-based tracking form

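### Changes from baseline to 12 and 18 months in one arm show whether participants are still above their starting level, not whether the 6-month gain was kept

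*Protocol article*

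**What the plan says.** The statistical analysis section of the protocol article gives the extra intervention-arm follow-up two uses. One is the feasibility of retaining participants. The other is to evaluate "within group change to 12 and 18 months to determine the sustainability of any positive changes" that followed the active phase.

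The same section defines the changes. The models will examine "changes within groups from baseline to 6 months (and to 12 months and 18 months for the intervention group", and "Time will be modeled categorically with indicator variables (with baseline as the reference category". Interpretation is to rest mainly on estimates and 95% confidence intervals, but there is also a labelling rule: "Confidence intervals for differences excluding zero or two-sided p-values less than 0.05 will be reported as statistically significant".

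Under Data collection, Outcome evaluation, outcomes are measured at baseline and 6 months in both arms, "then again at 12 and 18 months in the intervention group only". The comparator section explains why: "After the 6 month measurement sessions are completed, participants allocated to this group will be given the opportunity to start the 6-month" program. On timing, the Study design section says: "Study recruitment will begin in May 2015 at the 5 clinic sites, with the intervention starting in June 2015". No end of recruitment is given, and season is not mentioned.

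**The concern.** Whether a gain seen at month 6 persists is a question about what happens from month 6 onward. Every planned long-term contrast starts at baseline instead. Such a contrast can stay clearly positive after a large part of the gain has gone, so it does not answer the question asked.

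Two features make the reading harder. No comparator is observed after month 6, so drift from any cause stays in the estimate. And with a late-spring start, visits six or eighteen months apart fall in opposite seasons, which matters for step counts. The results are meant to inform optimization and scale-up of a program whose supports are withdrawn in stages, so a reader will look closely at how well the gain held.

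**Working it through.** **Planning figures.** From the Sample size section: effect size 0.65, SD 3498 steps/day, 38 evaluable per group, 30% dropout.

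- Per group: 2 × (1.96 + 0.8416)² / 0.65² = 37.2, rounded up to 38. With dropout: 38 / 0.70 = 54.3, rounded up to 55, or 110 in total. The stated sample size reproduces.
- Planning gain: 0.65 × 3498 = 2274 steps/day. This is a between-group effect, used here as a stand-in for the intervention arm's gain.

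**How much gain must remain for a baseline contrast to exclude zero?** SD of change = 3498 × √(2(1 − r)); SE = SD / √38; threshold = 1.96 × SE. The correlation r is not in the document, so a range is shown.

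| Assumed r | SD of change | SE | Threshold | Share of 2274 |
|---|---|---|---|---|
| 0.6 | 3129 | 508 | 995 | 44% |
| 0.5 (same as taking 3498 as the SD of change) | 3498 | 567 | 1112 | 49% |
| 0.3 | 4139 | 671 | 1316 | 58% |

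An observed remaining gain of 44–58% is therefore enough, so 42–56% could have gone. These are simple paired calculations; the planned mixed model would give somewhat different standard errors.

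**Chance of that happening.** Suppose half the gain is truly lost by month 12, so the baseline-to-12 change is 1137. With 38 participants (one-sample noncentral t), the 95% interval lies above zero with probability 0.50, 0.62 or 0.78 for an SD of change of 3498, 3000 or 2500. With no seasonal effect, the 6-to-12 contrast has an expected value of −1137 and shows the loss directly.

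**Season.** A May/June baseline puts months 6 and 18 in about November/December and month 12 back in May/June. Let S be an assumed drop in steps at the November/December visits; the document gives no value. With the gain fully kept:

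| S | Baseline-to-6 (within arm) | Baseline-to-12 | Baseline-to-18 | 6-to-12 | 6-to-18 |
|---|---|---|---|---|---|
| 0 | 2274 | 2274 | 2274 | 0 | 0 |
| 500 | 1774 | 2274 | 1774 | +500 | 0 |
| 1000 | 1274 | 2274 | 1274 | +1000 | 0 |
| 1500 | 774 | 2274 | 774 | +1500 | 0 |

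At an SD of change of 3498, the baseline-to-18 interval lies above zero with probability 0.97, 0.86, 0.59 and 0.26 down the rows, although nothing has been lost.

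If half the gain is lost by month 12 and stays lost, 6-to-18 is −1137 at every S. By contrast, 6-to-12 reads −1137, −637, −137 and +363. Only the 6-to-18 contrast reports the loss correctly whatever the season.

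**The case against.** The strongest reply has four parts.

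- **No verdict rule.** A reader might infer that the trial will declare success as sustained whenever a change from baseline is significant. The document does not say so. It puts estimates first, and changes at 6, 12 and 18 months share one reference, so a large fall would show in the planned output. This stands, but only partly. Comparing those estimates by eye gives no interval for the loss, and season can hide it. With S = 1000, the within-arm change at month 6 is 1274. If 44% of the gain is then lost, baseline-to-12 is 0.56 × 2274 = 1273, and the two planned estimates look like full maintenance.
- **Season is assumed.** A reader might infer that all the planned maintenance contrasts cross seasons. They do not: baseline-to-12 is one year apart. The size of any swing is not documented, and long recruitment would blur the pattern. It is also an argument about steps, not every outcome. All of this stands.
- **No attribution to withdrawn supports.** Supports end at month 12 ("Participants will no longer have access to the online Tyze Personal Networks, and Sykes phone coaching services"), so a reader might infer that a later drop will be blamed on that. The section only describes the phase; no such attribution is planned.
- **Scope.** This is a pilot whose single-arm follow-up is disclosed and follows from the wait-list design, and detailed contrasts can be left to an analysis plan. That is fair as to omissions. But the article does fix which changes will determine sustainability, and those do not match the question.

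**Conclusion.** The point holds as a mismatch between aim and contrast, and it does so even with no seasonal effect. At 38 participants, about 44–58% of a 2274-step gain is enough for a baseline-referenced interval to exclude zero. This rests on r between 0.3 and 0.6 (or 3498 taken as the SD of change), on the between-group planning effect as a proxy for the gain, and on the 6-month evaluable number. No retention figure for 12 or 18 months is given.

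The seasonal part is conditional on enrolment being concentrated near the May/June 2015 start. Under that condition it affects baseline-to-18 among the two planned long-term contrasts, but not baseline-to-12.

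Without a concurrent comparator, neither the planned nor the proposed contrasts can establish sustainability causally. The randomized 6-month comparison is not touched, since both arms are measured on the same schedule.

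**What to change.** From the same fitted model:

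1. Name the 6-to-18-month within-group contrast as the main maintenance estimate. Report 6-to-12 and the planned baseline-to-12 and baseline-to-18 changes alongside it, all with 95% confidence intervals.
2. State that sustainability will not be judged by whether a change from baseline is significant. Nor should a non-significant 6-to-18 change be read as proof of maintenance: under the same assumptions its interval has a half-width of about 995 to 1316 steps.
3. Replace the promise to determine sustainability with one to describe maintenance, giving the lack of a concurrent comparator as the reason.
4. For step counts, caution that the within-group baseline-to-6 change and the 6-to-12, 12-to-18 and baseline-to-18 changes may be affected by season. Show the comparator's baseline-to-6 change as a gauge of that drift.
5. Do not report a share of the 6-month gain retained that uses the within-group 6-month change as denominator. With S = 1000 and the gain fully kept, it would be 2274 / 1274, or about 1.8.

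The cost is a few contrast statements and some wording. The categorical-time model already supplies the estimates, and no data, visits or participants are added.

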### Sample size

We set a recruitment target of 110 participants. Baker and colleagues [31] conducted a 12-week RCT of a pedometer-based walking program plus PA consultation in 80 community-dwelling Scottish adults [mean (SD) age: 49.2 ± 8.8 years; 79% women] who were not meeting current PA recommendations (20% withdrawal rate by 12 weeks). After 12 weeks, this study reported a difference between intervention and control groups in mean change of 3021 steps per day – favouring the intervention group. Using a pooled standard deviation of 3498 steps per day results a Cohen’s d effect size of 0.86. In order to be conservative, we reduced the effect size to 0.65, a moderate to large effect size. Thus, with 38 participants per group, our study would have 80% power at a 0.05 two-sided significance level to detect an effect size of 0.65 [32]. We estimate a dropout rate of 30% over the 6-month period, which will increase our target to 110 participants (55 participants per group). Since we have 5 sites who expressed interest in taking part in this study, we propose that each site will need to enroll 22 participants (i.e., 11 participants per group per site).

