### Participant recruitment & enrollment

Participants will be recruited at the sites through poster advertisements, word of mouth, health care provider referrals, staff e-mails, and in-person recruitment booths. Those interested in participating will be contacted by the central research team and asked to attend an in-person screening session. At this session they will be screened for eligibility and if deemed eligible will take part in baseline measurements. Randomization will occur after baseline assessments. All individuals who contact a study site will be asked to report where they heard about the program. Participants who are ineligible and those who choose not to enroll in the study after initial contact will be tracked, along with reasons for ineligibility/not enrolling. Acceptability of randomization will be estimated from the percentage of participants who adhered to their allocation assignment (i.e., attend program sessions if allocated to the intervention group) and/or attend measurement sessions. Participation in the follow-up measurement sessions will be used to assess retention throughout the trial. Attendance at program sessions will be obtained from coach’s logs and will be used to assess adherence to the program.

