*Health-Related Quality of Life*		
Self-Rated Health [visual analog scale (VAS) score]	European Quality of Life 5 Dimensions Questionnaire - 3 Level Version (EQ‐5D- 3 L) [48]	• Self-completed paper-based questionnaire • For purposes of this study, the VAS score will be used to assess current state of health on a scale from 0 (worst imaginable state of health) to 100 (best imaginable state of health)

^a^METs (metabolic equivalents) are multiples of the resting metabolic rate; MET-minute = multiplying the MET score of an activity by the minutes performed

Average steps per day, measured using Yamax Digiwalker SW-200 pedometers and self-reported by participants using a 7-day paper log [41, 42] (at least 3 days of logging required).Total physical activity (Metabolic Equivalent (MET)-minutes/week) measured using the International Physical Activity Questionnaire (IPAQ) Short Form [43]; and time spent in sedentary activity (minutes spent sitting on a typical week day) measured with the IPAQ.Objectively-measured clinical characteristics: weight (using Tanita HD 351 Digital Weight Scale; kg and % of baseline weight), Body Mass Index (BMI, calculated from weight and height in kg/m^2^), waist circumference (cm) [44], and resting systolic blood pressure (BP) and diastolic BP (using BP Tru BPM-100; mmHg).Self-reported eating: healthful eating score, measured using Starting the Conversation (STC) questionnaire [45]; fatty food score, sugary food score, as well as fruit and vegetable consumption, measured using a modified version of the Dietary Instrument for Nutrition Education (DINE) [46] and following scoring outlined by Hunt and colleagues [47].Self-rated health measured using the European Quality of Life – 5 Dimensions – 3 Levels (EQ-5D-3 L) visual analog scale (VAS) score [48, 49].

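### The analysis set requires valid baseline data, although the chosen model can use randomised participants who have only a valid 6-month step count (minor)

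*Protocol article*

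**What the plan says.** All references are to the protocol article.

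- **Analysis set** (Data analyses, statistical analysis of the outcome evaluation): after naming an intent-to-treat approach, the article says "thus, we will include all participants with at least valid baseline data according to the randomization scheme".
- **Model** (same paragraph): a linear or generalised linear mixed model for repeated measurements, in which "we will retain the baseline outcome as part of the outcome vector and constrain the group means as equal because of randomization". The reason given for preferring it to analysis of covariance is that it "has the advantage of including subjects with missing data". On covariates: "Terms included in models will include time, treatment (group) × time, age and site".
- **Primary outcome** (same section): "The primary outcome will be the difference between the intervention and comparator groups in mean steps per day at 6 months".
- **Validity of a step count** (Data collection, Outcome evaluation): a 7-day paper log, with "at least 3 days of logging required".
- **Sequence** (Participant recruitment & enrollment): "Randomization will occur after baseline assessments". Neither the inclusion and exclusion criteria nor the section on randomization and allocation makes a valid step log a condition of being randomised.

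**The concern.** The set rule and the model pull in opposite directions. In an analysis of covariance, a missing baseline removes the participant because baseline is a covariate. Here baseline is one of the responses. The covariates that must be present are age, recorded at screening, and site, the randomisation stratum. A participant with only a 6-month step count can therefore be fitted, and that count is the datum the primary contrast needs. The rule removes the participant before the model is run.

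Such participants are foreseeable. The baseline step count depends on a self-completed paper log, and a log with fewer than 3 days is not valid. At stake are some primary-outcome values in a trial that already allows for 30% dropout, and the accuracy of the intent-to-treat label. The planned check on missing data compares dropouts with those analysed, so it is not aimed at people left out for an invalid baseline.

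**Working it through.** **1. The plan's own figure.** Inputs from Sample size: d = 0.65 (reduced from 3021/3498 = 0.86), two-sided 0.05, 80% power, 30% dropout.

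n per group = 2(1.960 + 0.842)²/0.65² = 15.70/0.4225 = 37.2, so 38. Power at 38 per group is 80.9% by the normal approximation and 79.9% by the noncentral t. Inflation: 38/0.70 = 54.3, so 55 per group and 110 in total. The article's statement that "with 38 participants per group, our study would have 80% power at a 0.05 two-sided significance level to detect an effect size of 0.65" and its target of 110 both reproduce. Expected 6-month values: 110 × 0.70 = 77, or 38.5 per group.

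**2. What the rule costs.** The documents give neither the share of invalid baseline logs (p) nor the baseline to 6-month correlation (ρ). Both are assumed. Invalid baseline logs are taken to be unrelated to dropout at 6 months. Outcomes are in units of the standard deviation at one time point.

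With equal arms, two time points and a common baseline mean, the variance of the 6-month difference is

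Var = 2 / [ n_both/(1 − ρ²) + n_6m-only ],

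where the counts are per arm. Participants with a baseline value only drop out of this expression. A 6-month-only record carries (1 − ρ²) of the information in a complete one. With n_both = 38.5(1 − p), and n_6m-only = 38.5p if these participants are kept or 0 under the rule,

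SE(rule)/SE(all kept) = √[ 1 + (1 − ρ²) · p/(1 − p) ].

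Example, p = 0.10 and ρ = 0.5: √(1 + 0.75 × 0.1111) = √1.0833 = 1.041.

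| p | 6-month values dropped (of 77) | SE excess, ρ = 0.3 | ρ = 0.5 | ρ = 0.7 |
|---|---|---|---|---|
| 2% | 1.5 | 0.9% | 0.8% | 0.5% |
| 5% | 3.9 | 2.4% | 2.0% | 1.3% |
| 10% | 7.7 | 4.9% | 4.1% | 2.8% |
| 20% | 15.4 | 10.8% | 9.0% | 6.2% |

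**3. Power at a difference of 0.65** (normal approximation; rule versus all kept):

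- ρ = 0.5: 90.3 v 90.7% (p = 2%), 89.4 v 90.5% (5%), 87.8 v 90.2% (10%), 83.8 v 89.4% (20%).
- ρ = 0.3: 81.0 v 84.5% (10%), 76.2 v 84.2% (20%).

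For p of 5–10%, power stays above 80% at every ρ examined. Of the combinations in the table, only p = 20% with ρ = 0.3 falls below it.

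**4. Check that the model runs with these participants.** In 200 simulated trials (55 per group, 10% of baselines and 30% of 6-month values missing by chance, ρ = 0.5, true effect 0.65), the mixed model with everyone kept used 77.6 six-month values on average, with mean estimate 0.661 and mean SE 0.198. With baseline-missing participants excluded it used 69.7, with mean estimate 0.666 and mean SE 0.207. The SE ratio agrees with the 1.041 above. Both estimates lie close to 0.65.

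**The case against.** **The link to the step log is an inference.** The set sentence does not define valid baseline data or refer to the 3-day minimum. It could mean one fixed set of people with a valid baseline assessment, in which case a poor step log alone would exclude nobody. This stands as a limit on what can be asserted. The sentence still fixes the primary analysis set and would then need a definition.

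**Few or none may be affected.** Randomisation follows baseline assessment, Table 1 places allocation at its own session, and the first coaching session uses the baseline step count. A valid log may be secured before allocation in practice, and a condensed article need not say so. This also stands: the number could be near zero.

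**The rule keeps what matters most.** Participants stay in their randomised groups, and those with a baseline but no follow-up are retained, so the model still handles the dropout that the plan expects. That is fair. But such participants add nothing to the precision of the 6-month difference in the formula above, whereas those removed would add to it.

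**Admitting people through a follow-up value conditions on something after randomisation.** This carries little weight. Under the present rule, too, the 6-month contrast rests on those who supply a 6-month value, under the same missing-at-random assumption.

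Three stronger readings are tempting and not supported. A reader might infer bias between arms, but on the documented sequence baseline validity is settled before allocation, so exclusion should not depend on arm. A reader might infer that the fault is a set that varies by outcome, but the text does not say that it does, and the contributing data would vary by outcome under the fix as well. A reader might infer that the sample size is wrong, but it reproduces.

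**Conclusion.** The point holds, as a minor one. The stated set is narrower than all randomised, which does not fit the intent-to-treat label, and it gives up the model's ability to use records with a missing baseline. If the baseline condition is applied to the step log, valid 6-month counts are discarded with no need.

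Under the assumed 5–10% invalid logs, about 4 to 8 of some 77 values are lost, and the standard error of the primary effect is roughly 1–5% larger than necessary for correlations of 0.3 to 0.7. These figures rest on assumed rates, on invalid baseline logs being unrelated to later dropout, and on reading the condition together with the 3-day minimum. The harm is modest precision and an inaccurate label.

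**What to change.** Replace the set sentence with wording such as: *All randomised participants will be analysed in the group to which they were allocated; every participant with a valid baseline or follow-up value of the outcome enters the mixed model.* State what counts as valid for each outcome, and say whether the 3-day minimum applies to the baseline step log. Keep the set with valid baseline values as a sensitivity analysis.

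The cost is a sentence or two and one extra model run. The model terms and the target of 110 do not change. The small downside is that missing baselines are then handled under a missing-at-random assumption, as the model already does for dropout. The sensitivity analysis shows whether that choice matters.

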Total physical activity (MET-min/week^a^)	International Physical Activity Questionnaire (IPAQ) – Short Form [43]	• Self-completed paper‐based questionnaire • Participants recall information on vigorous activities, moderate activities, walking, and sitting • Sedentary time is measured with a single question (minutes spent sitting on a typical week day) • The IPAQ provides guidelines for data processing and score creation
Time spent in sedentary activity (min/day)		
*Clinical Measurements*		
Weight (kg and percentage of baseline weight)	Digital Weight Scale (Tanita HD 351)	• Light clothing, no shoes and empty pockets • Blinded assessor post-baseline in private area
Body mass index (kg/m2)	Digital weight scale (Tanita HD‐351) Portable stadiometer (seca 213)	• BMI calculated using the participant’s objectively measured height and weight • Height measured without shoes
Waist circumference (cm)	Tape measure	• Follows protocol outlined by the Heart and Stroke Foundation of Canada [44] • Two measurements taken to record an average; if measurements differ by more than 5 mm, a third measurement is taken and used in the average
Systolic Blood Pressure (mmHg)	Digital BP monitor (BP Tru BPM-100)	• Participants sit quietly for 5 min prior to the first measurement; 3 measurements will be taken, 2 min apart. The first one is discarded, and the average of the last two is recorded. • Feet flat on the floor, arm free of clothing, cuff at the level of heart and arm resting, same arm used (left arm preferred), no talking
Diastolic Blood Pressure (mmHg)		
*Self-Reported Eating*		
Fatty Food Score	Modified version of the Dietary Instrument for Nutrition Education (DINE) [46]	• Self-completed paper-based questionnaire • Participants recall eating habits over the last 7 days • Methods published by FFIT will be followed to calculate a fatty food score (possible range 8–68) and sugary food score (possible range 3–16), with higher scores indicative of higher consumption • Fruit and vegetable consumption is measured with a single question
Sugary Food Score		
Fruit and vegetable consumption		
Total healthful eating score	Starting the Conversation [45]	• Self-completed paper-based questionnaire • Designed for dietary assessment and intervention in a clinical setting • Participants recall eating habits over the past few months (on average) on 8 different items • A total healthful eating score (possible range 0–16) is calculated, whereby a lower score indicates a more healthful diet

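### Weight as a percentage of baseline weight is a listed outcome, but the stated model keeps baseline in the outcome vector, where this measure equals 100 for everyone

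*Protocol article*

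**What the plan says.** Under Data collection, Outcome evaluation, Table 2 lists "Weight (kg and percentage of baseline weight" as a clinical measure. The list after the table repeats it as "kg and % of baseline weight". On timing: "The outcome measures will be taken at baseline and 6 months in both groups, and then again at 12 and 18 months in the intervention" (the article limits the two later visits to that arm).

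The analysis section (Outcome evaluation – statistical (quantitative) analysis) gives a single approach, linear or generalized linear mixed models for repeated measurements, in which "we will retain the baseline outcome as part of the outcome vector and constrain the group means as equal because of randomization". On model terms: "Terms included in models will include time, treatment (group) × time, age and site". On time: "Time will be modeled categorically with indicator variables (with baseline as the reference category". On scope: "For all secondary outcomes, we will also examine differences between intervention and comparator groups in mean change at 6 months" and "For all models, we will examine differences between groups at 6 months and changes within groups from baseline to 6 months". No outcome is exempted.

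The same section says that everyone with valid baseline data is analysed, that the approach is equivalent to analysis of covariance while keeping people with missing data, and that residuals will be checked. It names no covariance structure.

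**The concern.** The constrained-baseline model works because baseline varies between people and is correlated with follow-up. That correlation is what makes it behave like analysis of covariance. An outcome divided by its own baseline has neither property: each participant contributes a baseline row of exactly 100.

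Two stated elements therefore conflict, namely the outcome list and the model that covers it. An analyst who follows the text literally may get a fit that breaks down, or one that runs and treats constant baseline rows as information about residual variance. In the second case the confidence interval for the group difference is too narrow. This matters because the section bases interpretation on 95% confidence intervals and reports intervals excluding zero as statistically significant.

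**Working it through.** **Inputs from the article (Sample size).** 38 evaluable per group, 30% dropout, 55 per group, 110 in total. These reproduce:
- 3021/3498 = 0.864, reduced by the authors to 0.65.
- 2 × (1.96 + 0.8416)² / 0.65² = 37.15, so 38 per group (power 0.809 by normal approximation, 0.7985 by the noncentral t).
- 38/0.70 = 54.3, so 55 per group.

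The sample size concerns steps per day and is not in question. It only supplies the numbers for the check.

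**Assumed, because the article gives no values.** SD of percentage of baseline weight at follow-up, 5 percentage points (the SE ratios do not depend on it). Correlation between post-baseline visits, 0.7 or 0.9. No true group difference.

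**Step 1: baseline moments.** Y₀ = 100 × W₀/W₀ = 100 for everyone, so Var(Y₀) = 0 and Cov(Y₀, Y₆) = 0. A constant cannot act as a covariate, so there is no baseline adjustment.

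**Step 2: unstructured or visit-specific variances.** The REML log-likelihood was evaluated on one simulated data set (55 per group, 30% dropout, follow-up variance held at 25) as the baseline variance v₀ shrinks:

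| v₀ | log-likelihood | SE of group difference |
|---|---|---|
| 25 | −330.3 | 1.193 |
| 1 | −162.2 | 1.19 |
| 10⁻² | 77.3 | 1.19 |
| 10⁻⁴ | 316.8 | 1.19 |
| 10⁻⁶ | 556.2 | 1.19 |
| 10⁻⁸ | 795.7 | 1.19 |

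From 10⁻² downward, each 100-fold reduction adds about 239.5. That is (110 − 6)/2 × ln 100 = 52 × 4.605 = 239.5, from 110 baseline rows less six fixed effects (intercept, age, four site terms). The rise never stops, so there is no maximum. The SE of the group difference nevertheless stays near 1.19. A 6-month-only linear model had a mean SE of 1.15 over separately simulated data sets.

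**Step 3: common variance (random intercept or compound symmetry), analytic.** The estimated within-person covariance goes to about zero, and the variance is pooled over constant baseline rows and real follow-up rows.
- No dropout: pooled variance (0 + s²)/2. SE ratio √(1/2) = 0.71. Type I error 2 × [1 − Φ(1.96 × 0.7071)] = 0.166.
- 30% dropout: 110 baseline rows and 110 × 0.70 = 77 follow-up rows. Variance ratio 77/(110 + 77) = 0.412. SE ratio √0.412 = 0.64. Type I error 2 × [1 − Φ(1.96 × 0.6417)] = 0.21.

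**Step 4: the same structure by REML simulation** (55 per group, 30% dropout, adjusted for age and site):

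| Visits in model | Runs | Mean SE | Empirical SD | Ratio | Type I error | 6-month-only type I error |
|---|---|---|---|---|---|---|
| Baseline, 6 months | 1000 | 0.729 | 1.091 | 0.67 | 0.181 | 0.048 |
| Plus 12 and 18 months, correlation 0.7 | 400 | 0.802 | 1.129 | 0.71 | 0.150 | 0.052 |
| Plus 12 and 18 months, correlation 0.9 | 300 | 0.762 | 1.140 | 0.67 | 0.180 | 0.037 |

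The mean SE in the first row agrees with Step 3: 5 × √(2/38.5) × 0.6417 = 0.73, with 38.5 = 77/2 completers per group.

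**The case against.** The strongest reply is that the article names no covariance structure, which such an article may properly leave to the full protocol or analysis plan. The inflated error arises only with a common variance. The claimed equivalence to analysis of covariance suggests visit-specific variances and a free covariance, and there the SE can come out about right. This stands. The missing covariance structure is not itself a fault, and a reader might infer that the trial will report a false weight benefit, or that its intervals will be far too narrow. The documents do not support either inference.

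Second, the problem should be visible: a baseline column with no spread would show in a descriptive table, a degenerate fit would normally draw a software warning, and the residual checks should show baseline residuals unlike those at follow-up. This also stands, but the section names no replacement analysis, so one would be chosen after the data were seen.

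Third, the percentage is a second expression of one secondary outcome in a trial described as a pilot. Weight in kg, BMI and waist circumference have real baseline variance, fit the model, and would be reported beside it. That limits the damage without removing the conflict. An analyst might sensibly derive the percentage from the kg model, but the article does not say so.

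**Conclusion.** The point holds for one derived secondary outcome. As written, the model does not suit percentage of baseline weight under either usual family of covariance structures, and its stated equivalence to analysis of covariance is untrue for this outcome. Which failure would occur cannot be told from the article. Under a common variance, the SE ratio is 0.64 to 0.71 and the type I error is 0.15 to 0.18 in simulation, or 0.166 to 0.21 analytically. The upper end comes from the analytic approximation with 30% dropout. Under an unstructured covariance, the problem is degeneracy or non-convergence, not a small SE.

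The type I error figures rest on the article's own sample size and dropout, no true effect, and the assumed post-baseline correlations. Weight in kg, the primary steps outcome and the sample size are unaffected. The consequence is low to moderate, but the correction is cheap and worth making before analysis.

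**What to change.** State that percentage of baseline weight is excluded from the model that keeps baseline in the outcome vector, and name one of these instead:

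- **Log weight.** Fit log(weight in kg) in the same constrained model and report 100 × (exp(difference) − 1). Everyone with a baseline weight still contributes, and the equivalence to analysis of covariance is meaningful again. Cost: the result is a ratio of geometric means, not a difference in mean percentages, and should be labelled so.
- **Post-baseline percentage change.** Model percentage change at follow-up, adjusted for baseline weight in kg, age and site. This keeps the listed quantity. Cost: participants with no follow-up weight do not contribute, so for this outcome the stated advantage with missing data is lost.

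Either needs a sentence or two in the analysis plan and no new data. The kg analysis can stay as it is.
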